# Impact of externally facilitated continuous quality improvement cohorts on Advanced Access to support primary healthcare teams: protocol for a quasi-randomized cluster trial

**DOI:** 10.1186/s12875-023-02048-y

**Published:** 2023-04-11

**Keywords:** Advanced Access, Primary care, Continuous quality improvement, Audit and feedback, Interprofessional care

## Abstract

**Background:**

Improving access to primary health care is among top priorities for many countries. Advanced Access (AA) is one of the most recommended models to improve timely access to care. Over the past 15 years, the AA model has been implemented in Canada, but the implementation of AA varies substantially among providers and clinics. Continuous quality improvement (CQI) approaches can be used to promote organizational change like AA implementation. While CQI fosters the adoption of evidence-based practices, knowledge gaps remain, about the mechanisms by which QI happens and the sustainability of the results. The general aim of the study is to analyse the implementation and effects of CQI cohorts on AA for primary care clinics. Specific objectives are: 1) Analyse the process of implementing CQI cohorts to support PHC clinics in their improvement of AA. 2) Document and compare structural organisational changes and processes of care with respect to AA within study groups (intervention and control). 3) Assess the effectiveness of CQI cohorts on AA outcomes. 4) Appreciate the sustainability of the intervention for AA processes, organisational changes and outcomes.

**Methods:**

Cluster-controlled trial allowing for a comprehensive and rigorous evaluation of the proposed intervention 48 multidisciplinary primary care clinics will be recruited to participate. 24 Clinics from the intervention regions will receive the CQI intervention for 18 months including three activities carried out iteratively until the clinic’s improvement objectives are achieved: 1) reflective sessions and problem priorisation; 2) plan-do-study-act cycles; and 3) group mentoring. Clinics located in the control regions will receive an audit-feedback report on access. Complementary qualitative and quantitative data reflecting the quintuple aim will be collected over a period of 36 months.

**Results:**

This research will contribute to filling the gap in the generalizability of CQI interventions and accelerate the spread of effective AA improvement strategies while strengthening local QI culture within clinics. This research will have a direct impact on patients’ experiences of care.

**Conclusion:**

This mixed-method approach offers a unique opportunity to contribute to the scientific literature on large-scale CQI cohorts to improve AA in primary care teams and to better understand the processes of CQI.

**Trial registration:**

Clinical Trials: NCT05715151.

## Background

### Timely access in primary healthcare

Access is one of the major concerns faced by health systems worldwide. Access to health services is a high priority for the population, clinicians and decision-makers alike [1]. Timely access, such that patients can access the care they need when they need it, is one of the cornerstones of strong primary healthcare (PHC). Across Canada, timely access remains a major challenge. A recent international report documenting primary care access found that Canada ranks poorly compared to other high-income countries. According to a 2020 report by the Commonwealth Fund, only 41% of Canadians reported being able to get a same or next day appointment to see a doctor or a nurse the last time they needed medical attention [2]. This is a 5% decline since the previous report in 2016 [2]. Limited access increases the risk of poor health outcomes and health disparities [3, 4] and increases costs for the healthcare system.

### Advanced Access as a solution to improve access and continuity of care

Of the various organisational innovations developed to improve timely access to care, Advanced Access (AA) is one of the most recommended models [5]. Rooted in patients’ relational and informational continuity with a PHC professional/team to increase accessibility, the AA model ensures that patients obtain timely services based on their needs [6]. Originally developed in the United States in 2001, the effectiveness of the AA model, practiced among physicians and nurses, has been demonstrated in various healthcare systems [7–11]. Benefits of AA include reduced wait times [7, 9, 11–13] and missed appointments [7, 13] and improved professional and patient satisfaction [11, 14] as well as provider productivity [11].

Over the last two decades, AA has become increasingly popular in Canada. The model has been widely promoted by the College of Family Physicians of Canada and several other provincial organisations and professional associations [6]. Since the inception of the AA model 20 years ago, our research team has developed a revised model based on a more interdisciplinary team practice through a process of multiple consultations with 45 experts. The revised model is based on five key pillars: 1) comprehensive planning for needs, supply and recurring variations; 2) regular adjustment of supply to demand; 3) processes of appointment booking and scheduling; 4) integration and optimisation of collaborative practice; and 5) communication about AA and its functionalities [15]. The Fig. 1 presented the revised Advanced Access model.

**Fig. 1 Fig1:**
[figure not shown]
Revised Advanced Access model

Over the past years, the AA model has been implemented in Canada to varying degrees. On a more local level, the implementation of AA varies quite a lot among both providers and clinics [16, 17]. More importantly, our experience in the field shows that the model has not kept up with the development of PHC team-based approaches or with technological innovations [18]. Indeed, very few other PHC providers, such as social workers, psychologists and pharmacists, have implemented the model, despite its interprofessional scope. With the exception of an ongoing proof of concept led by our research team [19], the literature is scarce on strategies to expand the AA model to the entire PHC team.

### Continuous quality improvement (CQI) approaches

CQI approaches promote organisational change and are often based on improving specific processes, either by eliminating waste from the system (e.g. LEAN) or reducing variability and errors in the process (e.g. Six-Sigma). A widely used approach, the Model for Improvement [20], is designed to promote, structure and sustain changes in organisations to improve both processes and outcomes [21]. It aims to better understand the system itself, such as cultural or structural changes within the organisation, in order to implement a new model or new processes [22]. Following an investigation of a given problem, changes are implemented through iterative implementation cycles of four steps (represented by the acronym PDSA), [20] where change is: 1) planned based on evidence from data, community feedback and/or stakeholder experience (Plan); 2) carried out while documenting its effects (Do); 3) analysed by measuring the results achieved while comparing them to expected results and appreciating the impact of change (Study); and finally 4) refined, either by maintaining or adjusting actions in future cycles or by expanding its scale (Act).

### Factors and techniques for successful CQI

While CQI fosters the adoption of evidence-based practices [20] and is instrumental to achieve the quintuple aim, multiple strategies have been used to support organisational change [23, 24]. Despite emerging evidence on the influence of the implementation context on the outcomes of CQI [25, 26], such as managerial involvement [27], staff attitudes [27–29], interprofessional collaboration [28], effective communication [28], the presence of an internal champion [27], available resources [28], general QI culture [30], the absence of conflict [27], the QI objective itself [30] and fit with the organisation’s priorities [30], knowledge gaps remain, especially about the ideal team size and composition, optimal levels of patient involvement [31–33], and more importantly, the mechanisms [34–36] by which QI happens.

Continuing education alone or combined with other strategies cannot optimally achieve change without intensive follow-up [37, 38]. Experts internal or external to the organisation must accompany the process. This is called practice facilitation [37]. Practice facilitation is especially useful as a stand-alone intervention, compared to more limited strategies such as academic detailing or audit and feedback [37, 39]. Although practice facilitation can also be used effectively in combination with other strategies, studies have shown that tailoring facilitation interventions to the individual is a determining factor to achieve buy-in from stakeholders and, more generally, to implement changes in local settings [40–43]. Using external change agents in the practice facilitation model also appears to strongly facilitate organisational change, especially for smaller settings and PHC services [40–43]. Other enablers of practice facilitation include sustained interactions between facilitators and practices, appropriate and regular frequency of practice facilitation [44, 45] and patient and partner engagement [40–43]. In addition, support and coaching through multiple cycles [46] over a sufficient length of time (12–18 months) [47] are key to complete improvement cycles and achieve change goals [48].

Beyond practice facilitation, the scientific literature offers poor guidance on the criteria to select appropriate strategies to improve the *process* of CQI [49, 50]. This is largely due to the fact that such processes are often poorly defined in empirical studies and rarely or inadequately evaluated [36, 51–53]. This leaves implementers looking to design successful CQI initiatives with vague recommendations on the importance of supporting clinical teams over time through a personalised and evolutive approach focused on relationship building [36]. It is therefore complex to determine with certainty the causal links between CQI processes and their effects.

Studies showing the effectiveness of CQI also highlight its barriers, namely the complexity of healthcare organisations [25], the absence of structure or resources [25, 54, 55], poor understanding (and use) of CQI components [56] or support that is too succinct [25, 47]. Above all, successful CQI is time-consuming and resource intensive [57, 58]. Group mentoring, defined as ongoing group activities where participants with different levels of experience working in similar fields share their experience, increase their skills and take part in opportunities to reflect on their own practice [59], could accelerate PDSA cycles. This rapid knowledge transfer strategy could contribute to increasing the scale for tests of change and, consequently, the spread of successful implementation strategies [60]. In particular, sharing the optimal sequencing of tasks can help other teams plan their change strategies by building on what works or does not work in other teams [20]. Group mentoring through CQI cohorts could reduce isolation, bring new energy to QI strategies and improve knowledge about what works and what does not [61, 62].

Finally, studies focusing primarily on the sustainability of complex innovations supported through CQI are lacking [63, 64]. The few studies available underline the importance of focusing on the sustainability of the process up front, [65] adaptability of the CQI initiative [66] and relevance of the initiative for the organisation [66]. Identifying processes leading to long-term impacts of CQI is key to develop practical guidelines for healthcare teams who wish to improve patient care.

### Preliminary work: AA and CQI

Between 2008 and 2010, an Ontario-based CQI learning collaborative program (called QIIP) was available to all Family Health Teams, with some teams focusing, among other themes, on the improvement of their practice in AA. QIIP included three 2-day face-to-face learning sessions, action periods and a summative congress [67] offered in three waves occurring over about 15 months. The program failed to show significant differences between the intervention and control groups for most indicators, including the 3rd next available appointment [67]. Qualitative data suggested significant improvements in some practices, but also a high degree of variability among clinics. Of note, QIIP was successful in facilitating interdisciplinary team functioning. The QIIP team concluded that there was a need for further direct evaluation of QI approaches to improve AA in the future [67, 68].

The Quebec team members have developed extensive expertise and experience in assessing the implementation of AA among different PHC providers [69] and support individual reflection through the use of an online reflexive tool and a rigorous CQI process [19]. This intervention has shown an average decrease of 7 days to the 3rd next appointment and a decrease of 11% on the proportion of available time slots within the next 48 h. This project shed light on the fact that strategies to improve AA are often common across PHC teams and that there is a loss of efficiency when each provider and team are supported individually. Thus, we hypothesise that the addition of group mentoring would allow for system gains by allowing teams of providers 1) to have access to the strategies and learnings of other teams that have experienced it and 2) to share in real time with teams experiencing similar challenges.

There is great potential to improve access in PHC by supporting practices interested in improving AA and by expanding the implementation of the model to professionals other than physicians and nurses. The various AA projects conducted so far have 1) shown promising results and 2) contributed to the development of expertise and several tools to assess and guide the implementation of AA for all types of PHC providers. These findings guided our research team in the development and evaluation of a CQI cohort of PHC practices for the improvement of AA.

### Research objectives

We propose a multi-method quasi-randomised cluster trial to analyse the implementation and effects of CQI cohorts on AA for PHC clinics (see Fig. 2). Specific objectives are to:Analyse the process of implementing CQI cohorts to support PHC clinics in their improvement of AA.Document and compare structural organisational changes and processes of care with respect to AA within study groups (intervention and control).Assess the effectiveness of CQI cohorts on AA outcomes.Appreciate the sustainability of the intervention for AA processes, organisational changes and outcomes.

**Fig. 2 Fig2:**
[figure not shown]
Conceptual framework and research objectives

### Conceptual framework

The Informing Quality Improvement Research (InQuIRe) framework was chosen to guide this study [70, 71]. This framework is based on a literature synthesis of CQI theories and themes that have been adapted for PHC. The InQuIRe framework outlines (1) contextual factors at the organisational, team and individual levels; (2) the CQI process, including QI methods and teamwork; and (3) outcomes related to structural changes to organisations or processes of care and quality of care. Our hypothesis is that the proposed intervention will have a long-term impact on various AA processes, outcomes and organisational changes and that those will be influenced by contextual factors. The Fig. 2 shows the conceptual framework and the research objectives of the study.

## Methods

Based on the findings of other large-scale CQI initiatives [72], this study will be based on a quasi-randomised cluster-controlled trial allowing for a comprehensive and rigorous evaluation of the proposed intervention [73]. Such a design has been used to better understand both processes and outcomes of CQI [51]. Within the province of Quebec, clinics from randomly selected health regions will receive the intervention, while others will serve as controls (no CQI intervention). Intervention clinics will be matched with control clinics. The matching will be based on the clinic level (1 to 10, based on the number of patients registered and services offered) [74]. Clinics in the control group will receive an audit on a selection of AA indicators (Table 1) and will be offered the intervention 12 to 18 months following their recruitment.

**Table 1 Tab1:** Definition of AA measures

Measure	Definition

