### Sample size justification

The Quebec CQI pilot project showed that the average time to the 3rd next available appointment (primary outcome) is 11 days (sd = 10). Forty-eight clinics (clusters) averaging 15 professionals per clinic for a total of 720 professionals over six measurement time points will be measured every week or month (depending on the measure). An assumed intracluster correlation (ICC) of 0.364 (from the pilot project) provides about 80% power to detect a small effect size of 0.25 (Cohen’s d, assuming that variation will increase over the course of the intervention). This translates into a 50% reduction in time to the 3rd next available appointment from the baseline assessment [83]. Variations in clinic size have been considered (coefficient of variation of 0.49 according to the pilot project) [84]. No inflation for loss to follow-up is planned because the data is readily obtained from the EMR system for all professionals. Provision for one interim analysis 12-months post recruitment is planned using the Demets and Lan’s alpha spending function approach [85]. Thus, we aim to recruit 48 PHC clinics (24 interventions and 24 controls) for the trial proposed in this study.

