The impact of the intervention on AA outcomes (Obj. 3) will be structured around the quintuple aim [116]. For all outcomes, we will describe clinics and participants using means and standard deviations or medians and interquartile ranges. Also, time series analyses will be performed based on EMR indicators to detect changes since baseline, at the beginning of the intervention (T3), during the intervention (T3–T18) and the sustainability of the changes (T30). *Care team functioning*: To account for clustering of providers within clinics, the primary outcome measure, 3rd next available appointment, will be analysed using a generalised linear mixed model (with log link and quasi-Poisson distribution) adjusting for time to account for secular trends as well as important contextual factors such as number of providers and readiness for change. We will inspect missing data, and if more than 10% of the sample has missing values, we will use multiple imputation techniques. Otherwise, the maximum-likelihood method of estimation is considered adequate to address missing data in such regression models [117, 118]. Differences between the control and intervention periods and time trends will be estimated using odds ratios and their 95% confidence intervals. Similar regression models will be used (as dictated by the distribution of the data) to assess differences in % of 48-h open slots, walk-in usage, relational continuity and multidisciplinary involvement. *Patient experience*: A comprehensive description of patients’ experiences will be generated three times over the study. Items that focus on ease of access, perception of interprofessional collaboration, satisfaction with the appointment process and consultations outside the clinic for non-urgent care will be used for longitudinal analysis purposes. *Population health*: Discontinuity for chronic patients will be analysed using a generalised linear mixed model to assess the impact of the project on the management of chronic patients. *Health equity and inclusion*: Accessibility and patient experience will be stratified by visible minority status, ethnicity, preferred language, gender and physical or mental ability. If any disparity seems apparent, this issue will be addressed during the improvement efforts. *Efficiency:* Total costs to the system related to the implementation of the intervention as well as costs per clinic and cohort, accounting for different organisational characteristics, will be calculated. We will analyse the QI coach’s logbook to assign costs to the different tasks performed. Incremental ratios (i.e. change in costs to use the intervention divided by change in the 3rd next available appointment) will also be calculated.

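### Health regions are allocated, but the power calculation and the stated primary model stop at the clinic, so any correlation between clinics of one region would make the test too liberal

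*Protocol article*

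**What the plan says.** Three parts of the protocol article bear on this.

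- **Allocation.** The Methods section states that "clinics from randomly selected health regions will receive the intervention, while others will serve as controls (no CQI intervention". The abstract agrees on both arms: "24 Clinics from the intervention regions will receive the CQI intervention for 18 months" and "Clinics located in the control regions will receive an audit-feedback report on access". Matching of intervention to control clinics is on clinic level (1 to 10), not on region.
- **Power.** The sample size justification works with "Forty-eight clinics (clusters) averaging 15 professionals per clinic for a total of 720 professionals over six measurement time points". It uses one correlation, "An assumed intracluster correlation (ICC) of 0.364 (from the pilot project"), and a coefficient of variation of clinic size of 0.49. It concludes that this "provides about 80% power to detect a small effect size of 0.25". It gives no number of regions and no region-level correlation.
- **Primary model.** The Data analyses section introduces the generalised linear mixed model with "To account for clustering of providers within clinics". The adjustment terms it names are time, number of providers and readiness for change. Region is not named.

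**The concern.** The randomisation supports inference only at the level at which it was done. If whole regions are drawn, clinics in one region are not separate draws of the treatment. A clinic-level analysis takes the variation between clinics within an arm as its yardstick and counts 24 independent units per arm. When clinics of one region resemble each other, the difference between arms also carries the difference between the sets of regions that happened to be drawn, and the clinic-level standard error does not include it.

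Two things are at stake. The confidence interval and test of the primary outcome may be too optimistic, and so may the 12-month interim look at the same outcome. The stated power also rests on more independent units than were allocated.

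The other design features do not repair this. Matching on clinic level balances clinic size and services, not region. Adjusting for time removes trends common to both arms, not regional differences or region-specific trends.

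**Working it through.** **Inputs from the sample size justification:** k = 24 clinics per arm, m = 15 professionals per clinic, ICC 0.364, CV 0.49, d = 0.25, mean 11 days, SD 10. Two-sided 5% is assumed from the 95% confidence intervals in Data analyses.

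**1. The plan's own figure.** Design effect = 1 + [(1 + CV²)m − 1] × ICC = 1 + [(1.2401 × 15) − 1] × 0.364 = 7.41 (6.10 without CV). Effective number per arm = 360/7.41 = 48.6. Power for d = 0.25 is then 23% (27% without CV), not 80%. Six fully independent time points would give 85.5%. About 80% can be reached with repeated-measures correlations that the article does not state (one such setting gives 78.8%). So the 80% is not reproduced from the stated inputs, but it is not shown to be wrong either. The present point does not depend on it.

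**2. Adding the region.** In units of the total variance, the variance of a clinic mean is 7.41/15 = 0.494. Let R be the number of regions per arm, with 24/R clinics in each, and ρ the region share of variance; neither R nor ρ is in the document. Then

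true variance / clinic-level variance = 1 + (24/R − 1) × ρ / 0.494,

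type I error = 2 × [1 − Φ(1.96 / √ratio)].

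Example, R = 4, ρ = 0.05: ratio = 1 + 5 × 0.05/0.494 = 1.51, square root 1.227, and 2 × [1 − Φ(1.597)] = 0.110.

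| ρ (assumed) | Ratio, 4 per arm | Type I error | Ratio, 8 per arm | Type I error |
|---|---|---|---|---|
| 0 | 1.00 | 5.0% | 1.00 | 5.0% |
| 0.01 | 1.10 | 6.2% | 1.04 | 5.5% |
| 0.02 | 1.20 | 7.4% | 1.08 | 5.9% |
| 0.05 | 1.51 | 11.0% | 1.20 | 7.4% |
| 0.10 | 2.01 | 16.7% | 1.40 | 9.8% |

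Simulation of clinic means (20,000 trials per setting, t test on 46 df) agrees. For ρ = 0 / 0.02 / 0.05 / 0.10 it gives 5.1 / 7.5 / 11.1 / 17.7% with 4 regions per arm and 5.0 / 6.0 / 7.0 / 10.1% with 8.

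**3. Degrees of freedom alone.** Take an effect with about 77% power at clinic level. Here that is d = 5.5/10 = 0.55, half of 11 days over the SD of 10. It serves only as a reference point; the protocol's effect size is 0.25. The standard error is √(2 × 0.494/24) = 0.203, so the noncentrality is 0.55/0.203 = 2.71, and Φ(2.71 − 1.96) = 0.77 (0.76 from a t test on 46 df). With ρ = 0 and 2R − 2 degrees of freedom:

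- R = 4: 6 df, critical value 2.447, power 62%.
- R = 8: 14 df, critical value 2.145, power 71%.

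With ρ = 0.02 / 0.05 / 0.10, power is 55 / 46 / 36% (R = 4) or 68 / 63 / 57% (R = 8). Much of the loss at small ρ thus comes from the degrees of freedom, not from the region variance.

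**The case against.** **The article is condensed.** The number of regions and the full random-effects structure are often left to the full protocol or the analysis plan. The list of adjusters is open-ended, and the text does not say that clinic is the only level. This stands in part: a region term could appear elsewhere. But the article does commit to a cluster for the sample size, and that cluster is not the unit it allocates. A later analysis plan would not mend a sample size justified on the clinic.

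**The trial is longitudinal.** Six time points are planned and changes since baseline are to be detected. If the effect is estimated as change from baseline, stable differences between regions largely cancel, and only region differences in change over time matter. This stands as a limit on the figures above, which are cross-sectional. It does not remove the point: the article does not fix the contrast, and the Data collection section promises pre-intervention data explicitly only for the intervention group.

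**Stronger readings.** A reader might infer that the type I error is inflated as a matter of fact. The document does not show this; it needs a positive region-level correlation, which is not given. A reader might also suppose that clinics of one region share management, staffing or access policy. That is plausible, but nothing in the article says so, and the argument does not need it. Nor are the tabulated percentages this trial's error rates, since both R and ρ are assumed. Fewer regions than 4 per arm would be worse, and a smaller ρ would be milder.

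**Conclusion.** The mismatch holds: allocation is by region, power is by clinic, and the primary model as stated names clustering at the clinic only. The consequence is conditional. With any positive correlation between clinics of the same region (in level, or in change if that is the estimand), the clinic-level standard error is too small and the test is too liberal. With zero correlation the type I error stays at 5%, but the region-based power is still below the clinic-level figure. The amount of inflation cannot be settled from the document. The ranges in the working assume equal numbers of clinics per region and a single cross-sectional comparison of clinic means.

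**What to change.** - **Data analyses:** add health region as the top clustering level and test the group effect with small-sample degrees of freedom from the regions (total regions minus 2). A permutation test over the regional allocation is an alternative if there are enough regions. With 3 per arm there are 20 allocations and the smallest two-sided p is 2/20 = 0.10; with 4 per arm there are 70, and it is 2/70, about 0.029. The interim analysis should use the same test.
- **Sample size justification:** state the number of regions per arm, and restate power with region as the top level over a range of region ICCs, for example 0 to 0.10.

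The change to the text is small: one model term, a degrees-of-freedom rule and a revised power statement. The real cost is that the stated power becomes lower, and that a region variance is imprecisely estimated when regions are few.
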